One of the main challenges of Internet-based clinical interventions is the difficulty in establishing an adequate therapeutic bond, an essential component for successful psychological interventions. However, previous studies suggested that online therapies can establish satisfactory therapeutic alliances.^[30]^ Despite the great advances in the online treatment of depression, many aspects of these interventions require further study, such as the efficacy of online multimodal lifestyle programs for patients with TRD.

There is little scientific evidence supporting the benefits of an online adjuvant healthy lifestyle promotion program for patients with TRD, probably because implementation of these interventions is difficult.^[31]^ There is evidence that psychotherapy delivered by telephone or online may be useful for patients with depression, but less information is available regarding the use of Internet-based programs that focus on lifestyle in health emergency situations in which people are required to restrict their mobility and maintain physical distance.^[32,33]^ As far as we are aware, no previous studies have examined the effect of this approach for patients with TRD.

The main objective of this study is to analyze the effectiveness of treatment prescribed by the mental health team, written suggestions for lifestyle changes, and an 8-week lifestyle change promotion program in patients with TRD. There will be 2 control groups: a placebo control group will receive treatment prescribed by the mental health team and written suggestions for lifestyle changes; an active control group will receive treatment prescribed by the mental health team, written suggestions for lifestyle changes, and an 8-week iMBCT program, an intervention that has proven effectiveness in a face-to-face format.^[34,35]^

We hypothesize that patients randomized to the lifestyle intervention group will show significantly greater improvements in clinical measures of depression than patients from the 2 control groups at 12 months.

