### Outcomes measures

2.6

The primary outcome measure will be the severity of depression based on the Beck depression inventory-II (BDI-II). The secondary outcome measures will be the scores from scales that rate global clinical impression, quality of life, comorbidities, social support, mindfulness skills, physical activity, adherence to the Mediterranean diet, severity of insomnia, self-compassion, and acceptance and action.

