### Participant timeline

2.7

We will collect patient data using questionnaires administered at baseline (week-0), immediately after the intervention (week-8), at month-6, and at month-12 (Table 2).

**Table 2 T2:** Timeline for enrolment, allocation, interventions, and assessments.

	Study period				
	
	Enrolment	Intervention	Post-allocation		Close-out
				
Timepoint	−1 wk	0	8 wk	6 mo	12 mo
Enrolment					
Eligibility screen	X				
Informed consent	X				
Allocation		x			
Interventions					
MBCT intervention			x		
Lifestyles intervention			x		
Placebo		x			
Assessments					
Chronic conditions (ICD-10), BDI-II	x				
BDI-II, GCI, EQ-5D-3L			x	x	X
MOS-SS, IPAQ-SF, MEDAS, ISI			x	x	x

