### Sample size

2.8

Scientific evidence suggests that a 17% reduction in the BDI-II score^[38]^ is clinically relevant.^[64]^ A previous study by our team that examined psychiatric outpatients indicated the average BDI-III score at the beginning of the study was 24.5 (SD = 9.8).^[9]^ Thus, we considered a reduction of 6 points or more to indicate a clinically significant benefit. We estimate a maximum dropout rate of 25%. Accepting an α risk of 0.05 and a β risk of 0.15 in a bilateral contrast, 60 subjects will be required for each group. Thus, the total sample size will be 180.

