### Statistical analyses

2.11

All researchers conducting the data analysis will be blinded to group allocations. All eligible randomized patients who were evaluated at least once using the efficacy indicators will be defined as the “full analysis set”; all eligible randomized patients who attend at least 80% of the scheduled sessions will be defined as the “per-protocol set.” The effectiveness measurements will be evaluated mainly by intention-to-treat analysis using the full analysis set and supplemented by per-protocol analysis.

Numerical variables with normal distributions will be presented as means ± standard deviations, and categorical variables as absolute and relative frequencies. Numerical variables with skewed distributions will be presented as medians, minima, and maxima. Analysis of variance will be used to compare the 3 groups at multiple time points. In the main analysis, missing data will be replaced using multiple imputation. Complete-case analysis will be also conducted as a sensitivity analysis to assess the robustness of results from the multiple imputation procedure. Hypothesis testing will be performed using a 2-sided test and presented with 95% confidence intervals. A *P* value less than .05 will indicate statistical significance. All analyses will be performed using SPSS version 21.0 and STATA version 16.1.

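### The planned three-group ANOVA at several time points does not test the stated hypothesis that lifestyle is better than each of two controls at 12 months

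*Protocol article*

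**What the plan says.** The hypothesis closing the Introduction is that lifestyle patients "will show significantly greater improvements in clinical measures of depression than patients from the 2 control groups at 12 months". The Discussion repeats it for the end of the 12-month follow-up. That is two comparisons, each with a direction, at one time point.

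Section 2.6 (Outcomes measures) makes the BDI-II primary but attaches no time point to it. Section 2.7 (Participant timeline) places the follow-up assessments "immediately after the intervention (week-8), at month-6, and at month-12".

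Section 2.11 (Statistical analyses) says: "Analysis of variance will be used to compare the 3 groups at multiple time points". It adds: "Hypothesis testing will be performed using a 2-sided test and presented with 95% confidence intervals", and that a P "value less than .05 will indicate statistical significance". It names no lifestyle-versus-control contrast, no primary visit, and no rule on whether one or both controls must be beaten.

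Section 2.8 (Sample size) uses a 6-point difference, SD 9.8, alpha 0.05, beta 0.15 and at most 25% dropout, and concludes that "in a bilateral contrast, 60 subjects will be required for each group".

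**The concern.** An omnibus F test asks whether the three means differ in any way. The hypothesis asks whether one particular mean is better than each of the other two. The F test can be significant because iMBCT is better than the placebo control while lifestyle adds nothing, or because both programmes work equally well. The article itself describes MBCT as effective face-to-face, so these are patterns that the design should expect.

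The visits raise a second question. The hypothesis points to month 12, but the analysis section spreads the comparison over several time points with one P threshold and does not say which visit decides. The sample size rests on a single pairwise difference, so the quoted 85% power is not the power for being better than both controls. At stake is whether the main test, if positive, supports the claim that the trial was set up to make.

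**Working it through.** **Inputs.** From section 2.8: difference 6 points, SD 9.8, two-sided alpha 0.05, power 0.85, dropout up to 25%, 60 per group. From section 2.7: three follow-up visits. Assumed, because the article does not give it: correlation between follow-up visits, 0 to 0.7.

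**1. Reproducing the stated sample size.** For one comparison of two means:

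n = 2 × (1.960 + 1.036)² × 9.8² / 6² = 47.9, so 48 per group.

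48 × 1.25 = 60, the stated figure. It is therefore a two-group calculation for one contrast. With 25% dropout, 60 × 0.75 = 45 completers per group remain.

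**2. What the F test detects at month 12, 45 per group.** The noncentrality parameter is n × Σ(μᵢ − μ̄)² / SD². Means are written as lifestyle, iMBCT, placebo control; negative is better.

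- Only iMBCT works (0, −6, 0): the mean is −2 and the squared deviations are 4 + 16 + 4 = 24.
- Both programmes work equally (−6, −6, 0): the mean is −4 and the squared deviations are 4 + 4 + 16 = 24.
- Only lifestyle works (−6, 0, 0): again 24.

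In each case the noncentrality is 45 × 24 / 96.04 = 11.2. With 2 and 132 degrees of freedom this gives power of about 85%. The F test responds equally to all three patterns, and only the third fits the hypothesis. Simulation (20,000 trials per scenario, both lifestyle contrasts at two-sided 0.05) shows the gap:

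| True pattern at month 12 | F significant | Lifestyle significantly better than both |
|---|---|---|
| Only iMBCT works | 85% | 0% |
| Lifestyle and iMBCT equally effective | 85% | 2.5% |
| Only lifestyle works | 85% | 72% |

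**3. Error rate over visits, no true differences.** If a separate F test is read at .05 at each of three visits and the visits are independent, the chance of at least one significant result is 1 − 0.95³ = 14.3%. Simulation gives 13.5%, 12.8% and 11.2% at correlations 0.3, 0.5 and 0.7. One repeated-measures group-by-time test would stay at 5%.

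**4. Power for the hypothesis as stated.** Suppose lifestyle is 6 points better than each control.

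- 45 per group: 6 / (9.8 × √(2/45)) = 2.904, and 2.904 − 1.960 = 0.944, so power per contrast is 82.7%.
- 60 per group: 6 / (9.8 × √(2/60)) = 3.353, and 3.353 − 1.960 = 1.393, so power per contrast is 91.8%.

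The two contrasts share the lifestyle arm, so with equal groups their correlation is 0.5. Power for both, by simulation, is about 72% with 45 per group and about 86% with 60.

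**The case against.** The strongest reply has four parts.

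- **A significant F is not a false positive when iMBCT works.** The groups then do differ. Pairwise comparisons after a significant F are a standard route and, with three groups, control the error rate at one visit. This is right about the F test as such. But the plan names no such comparisons and no rule for reaching the lifestyle claim.
- **Contrasts and multiplicity may be in an analysis plan not shown.** That is possible, and silence alone would not be a finding. Here, however, the article states a hypothesis, a test, a threshold and a sample-size basis, and these do not fit together.
- **A reader might infer that the false-positive rate necessarily exceeds 5%.** The article does not support this. If both contrasts must succeed at month 12, no alpha adjustment is needed; in the simulation, lifestyle was declared better than both in about 0.5% of trials or fewer when no group differed. The 11–14% applies only if separate F tests are run by visit, which section 2.11 leaves open. Higher rates can be computed for unadjusted pairwise tests at every visit, but no section plans such tests.
- **A reader might also infer that the trial is too small for its ANOVA.** It is not: 45 per group gives about 85% omnibus power for a 6-point effect in one arm. The shortfall concerns the joint claim. Because 25% is given as the maximum dropout, the 72% is the low end of a range that reaches about 86%.

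**Conclusion.** The mismatch between test and hypothesis holds whether the ANOVA is run visit by visit or as one repeated-measures model. At month 12, with 45 completers per group and SD 9.8, the stated test is significant in about 85% of trials under two patterns in which lifestyle is not better than both controls.

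The error-rate part is conditional: about 11–14% for separate tests at three visits, under assumed correlations of 0.7 down to 0, and no inflation for a single repeated-measures test. Such a test would still not target month 12.

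The sample size serves one pairwise contrast. Power for both contrasts is about 72% to 86% across the dropout range, assuming a true 6-point advantage over each control. The article does not support a general statement that the trial's error rate is above 5%.

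**What to change.** - Name BDI-II at month 12 as the primary endpoint in sections 2.6 and 2.11.
- Make lifestyle versus placebo control and lifestyle versus iMBCT the primary contrasts, each at two-sided 0.05, and require both for the claim of being better than both. No alpha adjustment is then needed. A fixed order, placebo control first, is needed only if a claim against one control alone is also wanted.
- Label week 8, month 6, the omnibus test and iMBCT versus placebo control as secondary.
- State in section 2.8 that 60 per group refers to one pairwise contrast, and add the power for both: about 72% at 25% dropout and about 86% with none, if lifestyle is 6 points better than each control.

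The change is to wording only and uses the same patients, visits and data. It should be made before group allocations are unblinded. The cost is that the other visits and comparisons lose confirmatory status and the quoted power becomes less favourable.

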In addition to investigating the effect of modification of individual lifestyle factors, there has been progress in studying modification of combinations of lifestyle factors as a therapeutic tool for various medical conditions and mental disorders, such as depression.^[17–20]^ We recently tested a multimodal program that includes interventions that are particularly effective for patients with depression: daily physical activity, adherence to a Mediterranean diet, sleep hygiene, and regulated exposure to sunlight.^[21]^ Other studies also examined the effect of other interventions, such as promoting sociability and teaching emotional self-control techniques, that should also be considered.^[22,23]^ Some researchers proposed this approach as an alternative to psychotherapy or pharmacotherapy as the first treatment for depression.^[9]^ There is evidence that the clinical manifestations of depression decreased at 2 to 6 months after patients followed specific recommendations regarding improvements to lifestyle.^[9]^ However, this benefit subsequently disappeared, probably because of the limited duration of support, monitoring, and supervision.^[22]^ Group therapy has the potential to promote long-term adherence to an intervention program and improve patient outcome.^[24]^

Extensive scientific evidence indicates that online treatments for affective disorders are effective.^[25]^ The benefits of these treatments, compared with usual treatments, show a clear need to consider this approach in treatment guidelines for depression, regardless of symptom severity.^[26]^ Online treatments and teletherapy could therefore be a cost-effective alternative to traditional psychological care for the prevention of relapses and depressive episodes.^[27]^ The “Smile is Fun” program is an example of an effective online intervention that helped patients with moderate symptoms of stress and depression.^[27]^

Previous research of online psychological treatments mainly focused on Internet-based cognitive behavioral therapy (iCBT), and found that this was an effective and practical alternative to face-to-face interventions for treatment of depression.^[28]^ Some studies also demonstrated the effect of practicing mindfulness as an online treatment for depression.^[27]^ Moreover, a recent study reported that the combination of practicing mindfulness and iCBT (iMBCT) had potential for treatment of depression.^[29]^

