However, there are certain limitations that we must accept. All assessment instruments are self-applied to avoid possible assessor bias. However, it is not possible to blind study subjects in the 3 groups. Therefore, if patients aim to please the research team this could lead to response bias. To reduce this bias, we will inform all patients that each complementary treatment may be effective and will not explain our hypothesis regarding the potential greater long-term efficacy of the lifestyle intervention program. A second possible limitation is that certain elderly participants may have difficulties using ICTs. In these cases, we will recommend the assistance by family members. Another possible limitation is our uncertainty of the extent to which the COVID-19 pandemic will affect our study. In particular, a high infection rate could make it difficult to recruit participants and could also increase their stress, due to its adverse effects on health, income, and social factors, and thus hinder the efficacy of the treatment.

Despite these possible limitations, we believe it is urgent and necessary to develop an effective new intervention for patients with TRD who are facing uncertain and difficult situations, such as the COVID-19 pandemic.

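### The complete-case analysis named as the robustness check on the multiple imputation cannot detect dropouts who do worse than their observed data predict; a delta-adjusted analysis can

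*Protocol article*

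**What the plan says.** The Statistical analyses section (2.11) replaces missing data by multiple imputation in the main analysis. It does not describe the imputation model or state the missingness assumption. It then gives the robustness check to one method: "Complete-case analysis will be also conducted as a sensitivity analysis to assess the robustness of results from the multiple imputation procedure". The same section adds a per-protocol analysis of patients who attended at least 80% of sessions. That concerns attendance, not missing outcomes.

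The Sample size section (2.8) says "We estimate a maximum dropout rate of 25" per cent, without a split by arm. The hypothesis at the end of the Introduction compares the lifestyle arm with both control arms at 12 months, and assessments are planned at baseline, week 8, month 6 and month 12.

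**The concern.** A sensitivity analysis tests an assumption only if it relaxes that assumption. Standard multiple imputation takes a missing 12-month BDI-II score to be predictable from the patient's observed data. Complete-case analysis takes those who remain to represent those who left, which is at least as strong. If some dropouts have deteriorated in a way that their earlier scores do not show, both analyses miss it.

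At stake is the robustness statement in the final report. Two similar estimates would be presented as evidence that missing data did not matter, although neither addresses missing-not-at-random dropout. With up to a quarter of outcomes possibly missing a long time after an 8-week programme, a reader will want to know how far the result depends on that.

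**Working it through.** **Inputs from the article (section 2.8).** Difference of 6 BDI-II points ("Thus, we considered a reduction of 6 points or more to indicate a clinically significant benefit"); SD 9.8; two-sided α 0.05; β 0.15; at most 25% dropout; 60 per group.

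**The plan's own figure.** n = 2 × (1.960 + 1.036)² × 9.8² / 6² = 47.9, so 48 evaluable per group. Then 48 × 1.25 = 60, as stated. At 25% dropout, 60 × 0.75 = 45 per arm have an observed 12-month score.

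**Size of the bias.** Let d be the share missing in an arm and k the number of points by which its dropouts are worse than predicted. Subscript 1 is the lifestyle arm and 0 the comparator. Overstatement of the lifestyle effect = d₁k₁ − d₀k₀.

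| d₁ | d₀ | k₁ | k₀ | Bias (points) |
|---|---|---|---|---|
| 0.25 | 0.25 | 5 | 0 | 1.25 |
| 0.25 | 0.25 | 6 | 0 | 1.5 |
| 0.25 | 0.25 | 10 | 0 | 2.5 |
| 0.25 | 0.25 | 10 | 10 | 0 |
| 0.35 | 0.15 | 10 | 10 | 2.0 |
| 0.15 | 0.35 | 10 | 10 | −2.0 |

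The k values and the unequal dropout rates are assumptions. The last two rows show that the sign depends on which arm loses more patients.

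**Scenario A: loss leaves no trace at earlier visits.** Stayers in the lifestyle arm gain 6 points and its dropouts gain none. The true difference is 0.75 × 6 + 0.25 × 0 = 4.5. Simulation (60 per arm, SD 9.8, 25% dropout, 3,000 trials, 10 imputations from baseline and week 8) gave:
- all patients observed: 4.57
- complete-case: 6.04
- missing-at-random imputation: 6.04
- imputation with 6 points added to imputed lifestyle-arm values: 4.54

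Both planned analyses overstate by about 1.5 / 4.5, one third. The delta-adjusted analysis recovers the truth when the delta matches the assumed loss.

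A separate simulation (800 trials, 20 imputations; assumed correlations of 0.5 between baseline and later visits and 0.6 between week 8 and month 12) shows whether agreement is informative. The mean absolute gap between the two methods was 0.58 points with no shift and 0.57 with a 10-point shift in lifestyle-arm dropouts. Under this mechanism the gap carries no information about the bias.

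**Scenario B: loss partly visible earlier.** True difference about 4.5, month 6 added to the imputation model, and dropouts assumed to have been assessed at the earlier visits:

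| Loss visible | Complete-case | Imputation |
|---|---|---|
| Half at month 6 | 5.95 | 5.73 |
| Half at week 8, fully at month 6 | 5.98 | 5.28 |
| Fully at both | 5.93 | 4.97 |

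The methods now diverge, but imputation remains above 4.5.

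**Tipping point.** SE = 9.8 × √(2/45) = 2.07, and 1.96 × SE = 4.05. Adding δ to the imputed values of the 25% missing in the lifestyle arm moves the difference by 0.25δ. Significance is lost at δ = (observed − 4.05) / 0.25:
- observed 6: 1.95 / 0.25 = 7.8
- observed 5: 0.95 / 0.25 = 3.8
- observed 4.5: 0.45 / 0.25 = 1.8

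These are approximate, because the SE is held fixed as δ changes.

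**The case against.** **An unseen analysis plan may contain more.** The article calls complete-case one sensitivity analysis and does not rule out others. A reader might infer that the trial will run no other check; the article does not support that. What stands is narrower: the article itself names a method and gives it the task of showing robustness, and that method cannot do it for this kind of dropout. Comparing complete-case with imputation still has a limited descriptive use.

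**The two methods need not agree.** Scenario A is a worst case at the stated maximum dropout. Scenario B shows some divergence when earlier visits carry a signal. This is correct, but imputation stayed biased in all three variants, and a modest gap would not tell the reader how much bias remained.

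**Direction.** It is tempting to say that the bias must favour the programme arms. The documents do not establish this. Equal rates and equal shortfalls cancel. Lifestyle and iMBCT require the same time commitment, and the Discussion expects better adherence in the lifestyle arm; if retention follows, the bias against iMBCT could reverse.

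**Evidence that dropouts fare worse.** The Introduction says of earlier lifestyle studies: "However, this benefit subsequently disappeared, probably because of the limited duration of support, monitoring, and supervision". A reader might take this as showing that dropouts lose benefit relative to completers. It does not, because here programme sessions end at week 8 for everyone. Likewise, the Discussion's remark that "it is not possible to blind study subjects in the 3 groups" concerns response bias, not missingness. Leaving the sessions is also not the same as missing the telephone assessments. Informative dropout is therefore a possibility to be tested, not something the article demonstrates.

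**False positive.** Scenario A has a real 4.5-point benefit, so the effect is overstated, not invented. Creating significance from no true effect needs a large differential shift: with 10 points in lifestyle-arm dropouts only, both methods were significant for the intervention in about 19% of simulated trials, against 1.5% with no shift.

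**Conclusion.** The concern holds in a limited form. Assuming the usual missing-at-random imputation, agreement with a complete-case analysis is not evidence of robustness to dropouts who do worse than their observed data predict, and the article names no other analysis that would supply it.

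Bias arises only from a difference between arms in dropout rate or shortfall, and its direction is open, especially against iMBCT. Under the assumed scenario the overstatement is 1.5 points on a true 4.5. At 25% dropout, an observed 6-point difference would survive even complete loss of that benefit in lifestyle-arm dropouts (tipping delta 7.8), while observed differences of 5 and 4.5 would not survive a 6-point shortfall (3.8 and 1.8). Lower or more balanced dropout would shrink all of this. The change should be made because the weakness lies in a stated method and is cheap to remedy, not because a false result is likely.

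**What to change.** Keep multiple imputation as the main analysis and describe complete-case as a descriptive comparison. Pre-specify, before the 12-month data are analysed, a delta-adjusted (tipping-point) analysis of the 12-month BDI-II contrasts as the robustness check:
- add 0, 2, 4, 6 and 8 points to the imputed values in the lifestyle arm only;
- repeat with the same additions in both programme arms;
- report the delta at which each contrast loses significance.

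The grid reaches past 7.8, the approximate tipping point for the planned 6-point effect. The second set matters for the iMBCT contrast, where equal additions largely cancel if the two arms have similar dropout, so both sets should be shown.

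The cost is one or two sentences and a few extra runs on imputed datasets that are already planned, with no new data or patients. The downside is that the robustness statement may come out less favourable.
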